### Primary endpoint

Change of overall KOOS (Knee Injury and Osteoarthritis Outcome Score; group 1) or FOAS (Foot and Ankle Outcome Score; group 2) from baseline (Day 1 after operation) to Final Assessment (FA) 12 months after operation determined for each group and between the groups [14–18].

The KOOS or FAOS are patient-reported outcome measurement instruments. They are widely used in clinical trials, and its psychometric properties have been validated. They are available in a validated German version.

The KOOS or FAOS consist of five separately scored and validated subscales: Pain, Symptoms, Function in daily living (ADL), Function in Sport and Recreation (Sport/Rec), and knee/ankle related Quality of Life (QOL). The scores scale all range from 0 (worst outcome) to 100 (best outcome). For purpose of clinical trials, it has been recommended to create a composite score, by averaging the subscale scores of interest in the respective trial.

For further information see www.koos.nu.

### Secondary endpoint

Change of the 5 subscores of the KOOS or FAOS (Pain, other Symptoms, Function in daily living (ADL), Function in sport and recreation (Sport/Rec), knee/ankle related Quality of life (QoL)) from baseline (Day 1 after operation) to 6 and 12 weeks and 12 months after operation determined for each group and between the groups.

Circumference measurement of tights and lower leg on both legs 10 cm and 20 cm above the knee joint space and 10 cm below (knee in neutral position) from baseline (Day 1 after surgery) to day of discharge (7-11d), 3, 6 and 12 weeks and 12 months final assessment after surgery determined for each group and between the groups [3].

Range of motion (ROM) of the affected joint determined by neutral zero method from baseline (Day 1 after operation) to 6 and 12 weeks and 12 months after operation determined for each group and between the groups.

Short Form Health Survey (SF-36) from baseline (Day 1 after operation) to 6 and 12 weeks and 12 months after operation determined for each group and between the groups [19].

Dynamic gait index (DGI) from day of discharge (7-11d to 3, 6 and 12 weeks and 12 months after operation determined for each group and between the groups [20].

### Tertiary endpoint

Number of days of absence from work (employment) and/or days of inability to follow usual activities until final assessment and time point when patient was back to work and/or to follow usual activities. Data will be recorded for each group and compared between the groups.

### Hypothesis

Null hypothesis: There is no difference in overall KOOS (group 1) or FAOS (group 2) following rehabilitation with or without an anti-gravity treadmill (alter G®) 12 months after surgery.

### Statistical analysis

Demographic and clinical characteristics will be presented as means and standard deviations (SD) or frequencies and percentages, as appropriate. The normality of continuous data will be assessed by examining the histograms. If necessary, a suitable transformation will be considered to symmetrize the data.

Our primary efficacy endpoint for tibial plateau fractures/ankle fractures is change from baseline (first day postoperative) to 12 months in overall KOOS/FOAS. Literature data suggest a standard deviation of about 18 in KOOS4/FOAS. We expect a similar standard deviation for overall KOOS/FOAS. The developer of the KOOS/FOAS reports a minimally important change of 8–10 points.

We want to power this study to detect a moderate effect of 15 points using a two-sided *t*-test with a significance level of 0.05. With 25 patients per arm per group, we will have a power of 82% to detect a difference between groups of 15 points (48% power for a difference of 10). Using a one-sided *t*-test, the power figures are 89% (resp. 61%).

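### The primary endpoint is a change score, but its power uses an SD of 18 worded as the SD of the score; baseline-adjusted analysis of the 12-month score would protect the stated 82%

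*Protocol article*

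**What the plan says.** The Statistical analysis section of the protocol article defines the tested quantity as "change from baseline (first day postoperative) to 12 months in overall KOOS/FOAS". The Primary endpoint section also defines it as a change. The SD input follows directly: "Literature data suggest a standard deviation of about 18 in KOOS4/FOAS". It is then carried over to the endpoint's composite: "We expect a similar standard deviation for overall KOOS/FOAS".

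The design target comes next: "We want to power this study to detect a moderate effect of 15 points using a two-sided" t-test "with a significance level of 0.05". The stated power with 25 analysed per arm in each fracture group is 82% for 15 points and 48% for 10 points (one-sided: 89% and 61%). The Sample size section turns this into 60 randomised and 50 analysed per fracture group.

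The article gives no baseline SD, no correlation between baseline and 12-month scores, and no statement that 18 refers to a change. The t-test appears only in the power statement, and baseline adjustment is not mentioned. The Hypothesis section words the null in terms of the overall score 12 months after surgery, not in terms of change.

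**The concern.** The variance of a change depends on the SD at each visit and on the correlation between visits. A score SD can stand in for a change SD only if those three quantities happen to fit. The article uses 18 as though it were the SD of the tested quantity but words it as the SD of the instrument's score.

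If 18 is a score SD and the correlation is weak, subtracting the baseline mainly adds noise, and the printed power is too high. A weak correlation is plausible: the baseline is placed one day after fracture surgery and the outcome a year later. The documents give no figure for it, so it remains an assumption. At stake is whether 50 analysed patients per fracture group give the power claimed for the 15-point target. Power for 10 points, the upper end of the 8 to 10 point minimally important change that the article cites, is already stated as only 48%.

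**Working it through.** **Inputs from the Statistical analysis section:** n = 25 per arm, two-sided alpha 0.05, differences of 15 and 10 points, SD 18. **Assumed, because the article does not give them:** the correlation r (shown from 0 to 0.7) and the baseline SD (first set equal to 18, then varied).

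**1. Reproducing the stated power.** For a two-sample t-test with 48 df, the noncentrality is difference / (SD × √(2/25)). For 15 points this is 15 / (18 × 0.2828) = 2.95. Noncentral-t power is 82.3% for 15 points and 48.6% for 10 points (one-sided: 89.6% and 61.5%). These agree with the printed figures, so 18 was used as the SD of the quantity tested.

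**2. 18 read as the score SD at both visits.**
- SD of change = 18 × √(2(1 − r)). At r = 0.3: 18 × √1.4 = 21.3. It equals 18 at r = 0.5.
- ANCOVA residual SD = 18 × √(1 − r²), with 47 df. At r = 0.3: 18 × √0.91 = 17.2.

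| r | SD of change | Change t-test, 15 pts | ANCOVA SD | ANCOVA, 15 pts | Change t-test, 10 pts | ANCOVA, 10 pts |
|---|---|---|---|---|---|---|
| 0 | 25.5 | 53.3% | 18.0 | 82.3% | 27.5% | 48.6% |
| 0.2 | 22.8 | 62.6% | 17.6 | 83.8% | 33.1% | 50.2% |
| 0.3 | 21.3 | 68.4% | 17.2 | 85.7% | 37.0% | 52.3% |
| 0.5 | 18.0 | 82.3% | 15.6 | 91.5% | 48.6% | 60.3% |
| 0.6 | 16.1 | 89.8% | 14.4 | 95.0% | 57.6% | 67.2% |
| 0.7 | 13.9 | 96.1% | 12.9 | 98.1% | 70.0% | 76.8% |

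The ANCOVA column leaves out the small loss from chance baseline imbalance. On average this multiplies the variance by 1 + 1/(50 − 4), so at r = 0 the effective SD is 18 × √(47/46) ≈ 18.2 and power is 81.5%. Hence *about* 82%.

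**3. Unequal SDs.** With a 12-month SD of 18 and baseline SD s, the SD of change is √(s² + 324 − 36rs), which equals 18 at r = s/36. For s = 10, 12, 15, 20 and 22, the break-even r is 0.28, 0.33, 0.42, 0.56 and 0.61. With s = 10, the change t-test has 71% power for 15 points at r = 0 (SD 20.6), 79% at r = 0.2 (SD 18.8) and 83% at r = 0.3 (SD 17.8). The ANCOVA residual SD depends only on r and the 12-month SD, so its column does not move.

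**4. 18 read as the SD of change.** The change t-test has 82.3% power at any r. With equal SDs the score SD is 18 / √(2(1 − r)), and ANCOVA power for 15 points is 98.3% at r = 0, 94.7% at 0.3, 91.5% at 0.5 and 87.9% at 0.7.

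**The case against.** The strongest reply is that the article does not say what the 18 is. The SD sentence comes straight after an endpoint defined as change and shortly before a minimally important change. The literature source is not shown, so an SD of change cannot be excluded. That stands: the wording favours the score, but does not settle it.

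Several stronger readings are tempting, and the documents do not support them:

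- A reader might infer that 82% is right only at a correlation of exactly 0.5. With equal SDs, power is higher above 0.5. With a smaller baseline SD the break-even is lower, and under the change reading 82% holds at any correlation.
- A reader might infer that the trial is shown to be underpowered. That needs a weak correlation, for which the article gives no evidence. If patients score uniformly low the day after surgery, the baseline SD may be well under 18, and the loss is then smaller.
- A reader might infer that ANCOVA makes power independent of the correlation. It does not: power for 15 points still runs from 82% at r = 0 to 98% at r = 0.7. What goes is the loss below about 82%.
- A reader might infer that an unadjusted t-test is fixed as the primary analysis. It is named only for power, the article is condensed, and an analysis plan that is not shown could adjust for baseline.

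The last point limits the criticism of the analysis but does not dispose of it. A t-test, with change as the endpoint, is the only primary comparison the article names, and the power argument that sets the sample size is printed there. A later plan would not repair that argument. The move from KOOS4/FAOS to the overall score is openly stated as an expectation and is not counted here.

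**Conclusion.** The point holds in limited form: endpoint and SD do not demonstrably refer to the same quantity, so the 82% is conditional on something the article does not state. If 18 is the score SD at both visits, a t-test on change needs a correlation of at least about 0.5. At r = 0.3 the shortfall for 15 points is about 14 percentage points (82.3 − 68.4 = 13.9), and at r = 0 it is 29 (82.3 − 53.3 = 29.0). Above 0.5 there is no shortfall.

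Baseline adjustment is worthwhile under either reading, because its power for 15 points stays at about 82% or more. That floor assumes that 18 is the SD of the 12-month score or of the change; it would not hold if the 12-month SD were larger and 18 described only the baseline. Under randomisation, ANCOVA targets the same expected difference between arms as the change score does, so the 15-point target carries over. It also addresses the 12-month score on which the null hypothesis is worded.

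**What to change.** 1. State whether 18 is an SD of the score (and at which visit) or of the change.
2. Within each fracture group, make the primary comparison an ANCOVA of the 12-month overall score on arm and baseline overall score, reporting the adjusted difference with a two-sided 95% confidence interval.
3. Restate the power for 15 points as at least about 82% under ANCOVA (82% at r = 0, 86% at 0.3 and 92% at 0.5, with 18 as the score SD). If the change-score t-test is kept, show its power over a range of r and of baseline SD.
4. Before either, reconcile the baseline visit. The Primary endpoint and Statistical analysis sections place it on day 1 after the operation, whereas Table 2 marks KOOS/FAOS at the pre-operative 0d visit and not at +1d. Covariate and change score both depend on the answer.

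The cost is one degree of freedom, a sentence on the analysis and a revised power statement. It needs no further patients, and no measurement beyond the baseline the trial already plans once its timing is settled.

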### Sample size

According to statistical analysis of the primary endpoint following sample size was set.

To be allocated to trial (*n =* 120; group 1: *n =* 60 tibial plateau fractures, group 2: *n =* 60 ankle fractures)

To be analysed (*n =* 100; *n =* 50 tibial plateau fractures, *n =* 50 ankle fractures)

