### Inclusion and exclusion criteria

All patients will be assessed clinically preoperatively prior to inclusion to avoid subsequent exclusion. The definitive inclusion will be done after surgery and assignment to partial weight bearing of 20 kg for six weeks. Exclusion criteria are patients with more than 100 kg body weight, restriction of range of motion due to fracture morphology, serious illness or poor general health as judged by a physician that may influence the rehabilitation, open fractures (>1° according to Gustilo and Anderson) or surgical site infection which would cause a longer hospital stay, pregnancy, neuromuscular disorders, or preexisting muscle atrophy. Patients declining participation in the trial (and who fulfill the inclusion criteria) or withdrawing during the study will receive appropriate treatment according to the standard of care.

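### Read literally, the primary analysis is a complete-case t-test on change in 100 of 120 randomised patients, and the scheduled 6- and 12-week KOOS/FAOS go unused

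*Protocol article*

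**What the plan says.** All places are in the protocol article.

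- **Sample size.** The planned allocation is "To be allocated to trial (*n =* 120; group 1: *n =* 60 tibial plateau fractures, group 2: *n =* 60 ankle fractures". The next line reads "To be analysed (*n =* 100; *n =* 50 tibial plateau fractures, *n =* 50 ankle fractures". Both follow a lead-in that ties the numbers to the statistical analysis of the primary endpoint.
- **Statistical analysis.** The primary endpoint is the change in overall KOOS (tibial plateau) or FAOS (ankle) from the first postoperative day to 12 months. The test appears in the powering text: "We want to power this study to detect a moderate effect of 15 points using a two-sided *t*-test with a significance level of 0.05". Then: "With 25 patients per arm per group, we will have a power of 82% to detect a difference between groups of 15 points". No other inferential method is named.
- **Secondary endpoint.** The KOOS/FAOS subscores are assessed "from baseline (Day 1 after operation) to 6 and 12 weeks and 12 months after operation determined for each group and between the groups". Row E1 of Table 2 (Risk assessment) also marks KOOS/FAOS at 6 and 12 weeks. The overall score can be formed from the five subscales at each of these visits.
- **Primary endpoint and Table 2.** The endpoint text puts baseline at day 1 after the operation. Table 2 marks KOOS/FAOS at the preoperative visit and not at day 1.

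**The concern.** A t-test on observed change needs a baseline and a 12-month score. With 100 of 120 patients in that position, one randomised patient in six contributes nothing to the primary result, even where 6- and 12-week scores exist. Those scores are likely to say something about the missing 12-month value.

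Two things are at stake. One is precision: partly observed patients are discarded, and a change score is a less efficient use of baseline than adjustment for it. The other is bias. Patients know their arm because the treadmill replaces physiotherapy, and the outcome is patient-reported. Loss to follow-up could therefore depend on both arm and early recovery. If patients who recover poorly on the treadmill leave more often, the completers' difference favours the treadmill.

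**Working it through.** **1. The plan's own figures.** Inputs from Statistical analysis: SD 18, 25 per arm per fracture group, alpha 0.05, differences of 15 and 10 points.

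- Standard error of the difference: 18 × √(2/25) = 5.09.
- Noncentrality for 15 points: 15/5.09 = 2.95, with 48 degrees of freedom.
- Two-sided power from the noncentral t distribution: 82.3% (15 points) and 48.6% (10 points). Stated: 82% and 48%.
- One-sided power: 89.6% and 61.5%. Stated: 89% and 61%.

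The stated figures are reproduced.

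**2. The 120/100 split.** Per fracture group, 60 − 50 = 10 and 10/60 = 16.7%. In total, 20/120 = 16.7%. Conversely, 50/(1 − 1/6) = 60, so the split is exactly what an inflation for one-sixth loss would give. The article states no loss rate.

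**3. Power recovered from partly observed patients.** Assume that 25 of 30 per arm have a 12-month score and that all 30 have an earlier one. Let r be the correlation between the intermediate and the 12-month change; the documents give no value, so a range is shown. The variance factor per arm is (1 − r²)/25 + r²/30, and its inverse is the effective n.

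| r (assumed) | Effective n per arm | Two-sided power, 15 points |
|---|---|---|
| completers only | 25.0 | 82.3% |
| 0.3 | 25.4 | 82.9% |
| 0.5 | 26.1 | 83.9% |
| 0.7 | 27.2 | 85.5% |
| 0.8 | 28.0 | 86.5% |

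For example, r = 0.5 gives 0.75/25 + 0.25/30 = 0.0383, and 1/0.0383 = 26.1. The ceiling, with all 30 per arm seen at 12 months, is 88.8%.

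**4. Baseline adjustment against a change score.** Let the SD be σ at both time points and ρ the correlation between baseline and 12 months. The variance of the change is 2σ²(1 − ρ). The residual variance after baseline adjustment is σ²(1 − ρ²). The ratio is (1 + ρ)/2, which is below 1 for any ρ below 1: 0.60 at ρ = 0.2 and 0.75 at ρ = 0.5 (both values assumed).

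**5. Bias under one assumed dropout pattern.** Assumptions: SD 18 at each visit; correlation 0.6 between 12 weeks and 12 months; in the treadmill arm, 30% loss below and 3% above the 12-week mean; in the control arm, loss of one in six at random.

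- Share retained in the treadmill arm: (0.70 + 0.97)/2 = 0.835.
- Upward shift of the mean 12-week score in those retained: 0.798 × (0.97 − 0.70)/2 / 0.835 = 0.129 SD, or 0.129 × 18 = 2.3 points. Here 0.798 is the mean of the upper half of a standard normal distribution.
- Bias in the change: 2.3 × (0.6 − c), where c is the correlation between baseline and 12 weeks. This gives 1.4 points at c = 0, 0.9 at c = 0.2 and 0.7 at c = 0.3.

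Simulation agreed: about 0.6 to 0.7 points at c = 0.3, with close to zero bias for an estimator that uses the 6- and 12-week scores. With 50%/5% loss instead, the bias at c = 0.3 was about 1.3 points. For scale, 1 point is 1/5.09 = 0.2 standard errors, which raises a two-sided 5% error rate to about 5.4%.

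**The case against.** The strongest reply is that no completer analysis has been fixed. The 100 stands under Sample size, straight after a calculation with 25 per arm per group, and dividing by 5/6 gives 120 exactly. It reads naturally as evaluable patients plus an allowance for loss. The t-test appears only in the powering text, and powering on a t-test is routine even when the final model differs. The analysis set and the handling of missing scores are commonly left to the full protocol or SAP, which are not shown. All of this stands, so the exclusion of one in six is an inference and not a stated rule.

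The bias figure also rests on chosen inputs. The dropout pattern and the correlations have no source in the article. Because loss was made to depend on a score that the mixed model uses, the model's near-zero bias follows from that set-up. This stands too: the figure illustrates the risk and does not predict the bias.

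A reader might also infer that patients are removed after randomisation for infection, since one exclusion is "surgical site infection which would cause a longer hospital stay" and such an event can arise after day 1. The article does not support this. It lists infection among the eligibility criteria, places definitive inclusion after surgery, does not say when randomisation falls relative to an infection, and has no rule that takes randomised patients out of the analysis.

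What remains is narrower. The one inferential method the article does name makes poorer use of the scheduled data than a readily available alternative.

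**Conclusion.** This is an inexpensive improvement to the primary analysis; it does not correct an error. The article's wording, followed literally, gives a complete-case change-score t-test that leaves the 6- and 12-week KOOS/FAOS unused. The documents do not show that the sponsor intends to drop one in six randomised patients, and the trial is not underpowered on this account, since the stated power already rests on 25 per arm.

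The gain from the change is modest:

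- about 1 to 4 percentage points of power for 15 points, if the intermediate-to-12-month correlation is 0.3 to 0.8 and every patient missing at 12 months has an earlier score;
- a residual variance (1 + ρ)/2 times that of the change-score test, under equal variances;
- removal of a bias of roughly 0.6 to 1.4 points under one assumed arm-specific dropout pattern, small against the 8 to 10 point minimally important change that the article cites.

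**What to change.** - In Sample size, describe 100 (50 per fracture group) as the expected number with 12-month data, and state that all randomised patients enter the primary analysis in their allocated arm.
- Within each fracture group, take as primary the 12-month arm contrast from a repeated-measures mixed model on overall KOOS/FAOS at 6 weeks, 12 weeks and 12 months, with arm-by-visit and baseline-by-visit terms. A hospital term is optional.
- Keep the completer t-test on change as a sensitivity analysis.
- Before that, reconcile the baseline time point between the Primary endpoint section (day 1) and Table 2 (preoperative visit), because the model adjusts for it.

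**Cost.** Only the analysis wording changes; the 6-week, 12-week and 12-month scores are already scheduled. The model is somewhat more complex and assumes that scores are missing at random given those observed. It does not help patients lost before 6 weeks, who have no post-baseline score.

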### Risk assessment

Parallel to the study protocol a safety protocol was established. All patients will be examined pre-operatively for inclusion and during the hospital stay on the day after surgery and the day of discharge. Furthermore, clinical examinations will be done in the outpatient clinic after 3, 6 and 12 weeks and to FA (Table 2).

**Table 2 Tab2:** Summary of safety and efficacy study protocol

Summary of safety and study protocol								
		pre-operative entry examination	during hospital stay		out-patient clinic			
								FA
		0d	+1d	+7–11d	" + 3 we	+6we	+12 we	+12 mo
Safety	S1	x	x	x	x	x	x	x
	S2				x	x		
Efficacy	E1	x				x	x	x
	E2	x		x	x	x	x	x
	E3	x				x	x	x
	E4			x	x	x	x	x
	E5							x
S 1 = clinical examination			E 1 = KOOS/FOAS					
S 2 = interview before and after alterG training			E 2 = measuring circumference and joint mobility with neutral zero method					
			E 3 = SF −36					
			E 4 = Dynamic Gait Index (DGI)					
			E 5 = days of absence from work/registration of vocational retraining					

d = day, wk = week, mo = month, FA = final assessment

All adverse or severe adverse events will be recorded. So far, with the anti-gravity treadmill, no adverse events or severe adverse events have been described. After every training patient will be interviewed by the physiotherapist and heart rate, blood pressure, body weight, numeric rating scale (NRS), pain medication and general condition will be documented.

## Discussion

To date, no published randomized controlled trial with an anti-gravity treadmill is available. Two ongoing studies can be found for postoperative indications (NCT01689922, NCT02628002) and one dealing with the topic of postoperative treatment after total knee arthroplasty (NCT02426190). A recent study by McNeill et al. stated that there are significant differences between reported and measured body weight support on the anti-gravity treadmill [21]. Thus it could be possible that during training in the treadmill with 20 kg body weight partial loading might be higher than 20 kg. Several studies showed that the majority of patients could not reproduce accurately partial weight bearing and exceeded their target load with about 20 kg over target load [22–24]. Hence we accepted a possible inaccuracy of the treadmill since it is known that patients cannot put partial weight bearing of 20 kg into practice. Furthermore, an unintentional overload by the patient while walking with crutches is possible and unavoidable in both groups. A possible variance due to inaccuracy of the antigravity treadmill could be present.

The findings of this study can help to modify the rehabilitation of patients with partial weight bearing due to their injury or postoperative protocol. It will deliver interesting results if an anti-gravity treadmill is useful in rehabilitation in those patients. Further ongoing studies will prove different indications for an anti-gravity treadmill. Thus in connection with those studies a more valid statement due to safety and efficacy is possible.
